**Secondary outcomes**

1. **Disease-free survival**，calculated from the time of randomization to date of first recurrence or death from any cause. Disease-free survival will be compared 3 years after the recruitment.
2. Perioperative morbidity and mortality, and oncologic efficacy will be compared when the last patient discharged.
3. Locoregional recurrence and recurrence pattern will be compared 3 years after the recruitment.

All data analyses will be performed with the statistical package SPSS. A *P* value of <0.05 is considered statistically significant.

- 1. Chi-square or Fisher’s exact test will be used to compare categorical data.
  2. Student’s t-test or the Mann-Whitney U test will be used for continuous data.
  3. The Kaplan-Meier method will be used to estimate survival, and the log-rand test will be used to determine significance.
  4. Multivariate Cox regression analysis will be used to identify the risk factors related to overall survival. Multivariate Logistic regression analysis will be used to identify the risk factors related to cervical lymph nodes metastasis.

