**RESPONSIBLE PARTY**

[name] MD.

*This study was discussed in the Multidisciplinary Treatment Team for Thoracic cancer, approved by the Institutional Review Board of Fudan University Shanghai Cancer Center, and registered in Clinicaltrial.Gov under number NCT01807936.*

1. **Background:**

Esophageal carcinoma is an aggressive disease with a poor prognosis. Surgical resection with radical lymphadenectomy remains the basic method of management of this malignancy. Lymph node metastasis is one of the important factors in predicting the prognosis of patients with esophageal carcinoma, but the extent of lymph node dissection is still in debate. In the randomized trial of transhiatal compared with transthoracic esophagectomy for adenocarcinoma from the Netherlands, patients with positive lymph nodes potentially benefited from transthoracic esophagectomy with radical lymphadenectomy) (Hulscher JB, N Engl J Med. 2002). However, cervical LNM are common in esophageal cancer, with the incidence more than 20%. To improve the survival, three-field lymphadenectomy was developed to remove all potentially positive lymph nodes in the neck, mediastinum and upper abdomen. However, the value of three-field lymphadenectomy remains controversial due to the lack of prospective evidence. To date, only 2 randomized trials compared three-field lymphadenectomy and two-field lymphadenectomy, but the results are conflicting and the studies underpowered (Kato H, Ann. Thorac. Surg. 1991; Nishihira T, Am. J. Surg. 1998.)

1. **Purpose:**

The purpose of this study is to test two different extents of lymphadenectomy (Cervical-thoracic-upper abdominal three-field lymphadenectomy and thoracic-upper abdominal two -field lymphadenectomy) for patients with thoracic middle and lower esophageal cancer. This research is being done to see whether one extent of lymphadenectomy is superior than the other with better long-term outcome and acceptable postoperative short-term outcome or not.

1. **Trial:**
2. Allocation: Randomized (sealed envelope method).
3. Endpoint Classification: Efficacy Study.
4. Intervention Model: Parallel Assignment.
5. Masking: Open Label.
6. Primary Purpose: Treatment.
7. Single-institutional.
8. **Study protocol:**

[figure not shown]

Figure 1. Screening, randomization, follow-up and explorative sequencing of the patients.

**4.1 Estimated Enrollment:** 400.

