PASS (power analysis and sample size software) were used for sample size calculation. Previous data indicated a 15% difference in 5-year survival between two-field lymphadenectomy (30%) and three-field lymphadenectomy (45%). With a three-year accrual and an estimation of 10% loss of follow-up, 200 patients per study arm were necessary, using 80% statistic power.

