***Inclusion Criteria:***

1. Patients with histologically proven esophageal cancer
2. Patients with cT1-T3/N0-N1 mid or distal third (inferior to carina and 3cm superior to cardia ) operable esophageal lesion. Staging investigations including esophagogastroscopy, chest and abdominal CT scan, barium swallow and selective endoscopic ultrasonography showing no evidence of invading adjacent structure such as spine, bronchus, pericardium, descending aorta and without enlarged cervical and celiac nodes (diameter of short axis greater than 1.5cm) measured at CT scans.
3. Karnofsky performance status greater than or equal to 80%
4. Pulmonary and cardiac function must be acceptable for surgery according to institutional standards.
5. Acceptable hepatic, renal and bone marrow function

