**Primary outcome**

**Overall survival**, calculated from the time of randomization to death from any cause or the time to the last follow-up visit. Overall survival will be compared 3 years after the recruitment.

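### The overall survival comparison is an unadjusted log-rank test; pre-specified adjustment for clinical T, clinical N and tumour location could gain power at little cost and would name a hazard ratio

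*Protocol*

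**What the plan says.** The protocol has its own section titled Statistical analysis plan. Overall survival is the primary outcome, and its timing is given under Primary outcome: "Overall survival will be compared 3 years after the recruitment". The list of methods at the end of that section supplies the test: "The Kaplan-Meier method will be used to estimate survival, and the log-rand test will be used to determine significance" (log-rank is plainly meant). The threshold is a P "value of <0.05 is considered statistically significant". No strata, covariates, hazard ratio or confidence interval are named for the arm comparison.

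A Cox model does appear, with a different task: "Multivariate Cox regression analysis will be used to identify the risk factors related to overall survival". Neither the treatment arm nor any covariate is listed for it.

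The inclusion criteria in section 4.5 admit "Patients with cT1-T3/N0-N1 mid or distal third" lesions, so clinical T, clinical N and location must be on record before a patient is randomised. Section 4.2 describes sealed envelopes prepared by a biostatistics department and says nothing about stratification.

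**The concern.** Baseline information that may predict survival is already in hand, yet the primary test does not use it. If these factors are prognostic, an analysis that includes them detects the same survival difference with higher probability from the same patients.

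Two further points follow from how the Cox model is described.

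- **No between-arm estimate is named.** The stated purpose weighs long-term benefit against short-term harm. That judgement needs the size and precision of the survival difference as well as a P value.
- **The covariates are left open.** If an adjusted arm effect were later taken from the risk-factor model, its covariates could be chosen after the data are seen. They could include pathological nodal status. How many positive nodes are found depends on how many are removed, and that is the randomised intervention, so adjusting for it would distort the comparison.

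**Working it through.** **Inputs from the protocol.** Section 4.1 gives five-year survival of 30% (two-field) and 45% (three-field), three-year accrual, 10% loss, 200 per arm and 80% power. The significance level is 0.05. The analysis is timed three years after recruitment.

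**Assumptions.** The test is two-sided (the protocol does not say). Survival is exponential, so follow-up of 3 to 6 years per patient gives the event counts below. The 10% loss is taken as 400 × 0.9 = 360 evaluable patients.

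**Step 1: the plan's own sample size.**
- Two-proportion formula without continuity correction: n = [1.96·√(2 × 0.375 × 0.625) + 0.8416·√(0.30 × 0.70 + 0.45 × 0.55)]² / 0.15² = 163 per arm.
- With continuity correction: 176 per arm.
- Allowing for loss: 176 / 0.9 = 196, within 3% of the stated 200. The sample size is not in question.

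**Step 2: power of the planned log-rank test.**
- Design hazard ratio: ln(0.45)/ln(0.30) = 0.663, so ln HR = −0.411.
- Average event probability with 3-year accrual plus 3-year follow-up: 0.581.
- Expected events: 360 × 0.581 = 209; 400 × 0.581 = 232.
- Schoenfeld power: Φ(√events/2 × 0.411 − 1.96), which is Φ(1.01) = 84% with 209 events and Φ(1.17) = 88% with 232.

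**Step 3: power with adjustment.** The protocol gives no prevalence or hazard ratio for the three factors, so a range was simulated. There were 4,000 trials per scenario and 360 patients per trial, with marginal five-year survival held at 30% and 45%. Assumed prevalences were cT3 50%, cN1 40% and lower third 40%. The stratified test used all three factors. Monte Carlo standard error is about 0.6 points or less.

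| Assumed HR for cT / cN / location | Unadjusted log-rank | Stratified log-rank | Adjusted Cox | Cox gain (points) |
|---|---|---|---|---|
| 1 / 1 / 1 | 83.7% | 82.3% | 83.5% | −0.2 |
| 1.5 / 1.5 / 1.2 | 85.4% | 85.6% | 86.9% | +1.5 |
| 2 / 2 / 1.3 | 85.6% | 90.5% | 91.4% | +5.8 |
| 2.5 / 2.5 / 1.5 | 87.7% | 94.3% | 95.2% | +7.5 |

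Comparisons should be made within a row. Because the marginal survival rates are held fixed, the covariate-conditional treatment hazard ratio moves down the rows: 0.663, 0.651, 0.629 and 0.604.

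**Step 4: type I error.** With no treatment effect, rejection rates for the three tests lay between 4.9% and 5.2%, both with factors of no prognostic value and with hazard ratios of 2 / 2 / 1.3.

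**Step 5: chance imbalance.** Under simple randomisation of 200 per arm, a factor with 50% prevalence has a between-arm difference with standard deviation √(2 × 0.25/200) = 5 points. A difference of 8 points or more (z = 8/5 = 1.6) has probability about 11%. If that factor had a hazard ratio of 2, the log hazard ratio for treatment in that one trial would shift by roughly 0.08 × ln 2 = 0.055, about 13% of 0.411.

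**The case against.** The strongest reply is that nothing here is wrong. An unadjusted log-rank test is a standard and valid primary test in a randomised trial, its type I error is correct, and it exceeds the 80% target without help. That stands, and it rules out calling this an error.

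Several stronger readings are tempting, and the protocol does not support them.

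- **That the trial is underpowered.** The Background uses that word of two earlier randomised trials. Steps 1 and 2 show that it does not apply to this design on its own assumptions.
- **That the three factors are strongly prognostic.** The Background says so only of lymph node metastasis, which is not the same as clinical N stage from imaging. Nothing is said of the prognostic weight of clinical T or location. The power gain is therefore conditional and could be nil.
- **That randomisation was unstratified.** Section 4.2 is silent on strata; silence does not settle it.
- **That chance imbalance biases the test.** It is already part of the test's null distribution. Step 5 describes what can happen in a single trial and is an argument for efficiency only.
- **That the result will be a bare P value.** Kaplan-Meier estimates give survival by arm, and the Cox model does not exclude arm. What is missing is a named between-arm estimate with an interval.

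It can also be said that covariate lists and reporting details belong in a separate statistical analysis plan, which is not shown and may contain them. That has force for the detail. It does not dispose of the point, because the protocol's own analysis section fixes the test and assigns the Cox model a different purpose.

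**Conclusion.** The point holds as an improvement in efficiency and reporting. The planned log-rank test is valid and has about 84% power with 360 evaluable patients. Pre-specified adjustment in a Cox model would change power by about 0 to +7.5 points and leave type I error at about 5%. In the scenarios tried, the adjusted Cox model lost essentially nothing when the factors carried no information (83.5% against 83.7%).

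The size rests on assumed covariate hazard ratios of 1 to 2.5, assumed prevalences, a two-sided test, and follow-up of 3 to 6 years per patient. The documents cannot narrow the range. The case for a named hazard ratio with its interval, and for closing off adjustment by pathological nodal status, does not depend on those assumptions.

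**What to change.** Before outcomes by arm are examined, amend the analysis section along these lines:

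- **Primary comparison.** Overall survival in all randomised patients, by a Cox model with arm plus baseline clinical T (T1-2 or T3), clinical N (N0 or N1) and location (middle or lower third), reporting the hazard ratio and 95% confidence interval. The alternative is a log-rank test stratified by clinical T and N, with a matching Cox model for the hazard ratio. Name one of the two as primary.
- **Covariates.** Use only clinical stage recorded before randomisation, and state that pathological nodal status is not an adjustment factor. Define the boundary between middle and lower third; the inclusion criteria give only the outer limits of the eligible segment.
- **Supportive analyses.** Keep the Kaplan-Meier curves and the unadjusted log-rank test.
- **Disease-free survival.** Apply the same approach.
- **Risk-factor model.** Keep it as a separate, exploratory analysis.

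The cost is wording; no new data are needed. There are two drawbacks. The hazard ratio becomes conditional on the covariates, so it no longer corresponds directly to the 30% versus 45% design difference; the retained Kaplan-Meier estimates cover that. A stratified log-rank test could also lose about 1 point of power if the factors are not prognostic (82.3% against 83.7% when stratified by all three; stratifying by two was not simulated).
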